### Rigour

This protocol study also follows the evidence-based recommendations of The SPIRIT 2013 Statement for the minimum content of a clinical trial protocol. And the design of the study also follows the evidence-based, minimum set of recommendations of the CONSORT 2010 Statement for conduct parallel-group randomized controlled trials (RCT), enabling readers to understand a trial’s design, conduct, analysis and interpretation, and to assess the validity of its results.

Data availability: Upon completion of the study, the data gathered herein will be made available to those investigators who request it through FAIRsharing of the repositories of research data at https://www.re3data.org/.

## Discussion

Cancer-related asthenia is considered the most common symptom associated with tumours and their treatment and is an essential factor in the functional deterioration of individuals with cancer [5]. There is growing interest in conducting clinical trials on the influence of physical exercise on the quality of life of cancer patients, although how these beneficial influences might affect the autonomy of patients in their daily lives remains to be addressed. However, these beneficial effects have been observed in daily clinical practice in patients with cancer-related asthenia in terms of physical improvements. Nonetheless, difficulties in generalising this physical improvement to occupational performance have also been noted [7–9].

As oncological clinicians, one of the biggest problems we face on a daily basis is that, although the acute patient symptoms will have been optimally resolved at the time of hospital discharge, there is still room for improvement in functional terms. With the planned follow-up described in this article, we intend to resolve this handicap by incorporating a prescription for specific rehabilitation methods for patients. We consider it essential to include ADL re-education techniques as part of the multimodal physical exercise rehabilitation methods [9].

Furthermore, in order to favour both an adequate intervention environment as well as self-management of situations by patients, our study proposes a supervised home-based intervention adapted to the specific situation of each patient with moderate cancer-related asthenia for implementation after their discharge from hospital. This meets the NCCN recommendations that better, more accessible physical exercise programs should be offered which patients are able to easily adhere to. In addition, they also suggest that the prescription of support products should be incorporated as these will contribute to achieving greater immediate functional improvement of individuals.

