The available scientific literature indicates that the efficacy of these physical exercise interventions to address cancer-related fatigue is increased when a psychological component is added, especially when a interdisciplinary (oncology, nursing, physiotherapy, occupational therapy, and medicine) biopsychosocial approach is taken [13, 14]. Thus, different aspects related to loss-of-function, pain, and fatigue associated with fear-avoidance disorders should also be explored and evaluated by testing the degree of kinesiophobia in patients with cancer [15]. The cognitive-behavioural model of fear of movement notes that patients with chronic pain or fatigue syndrome tend to avoid physical activity because they believe that this activity causes or exacerbates these symptoms; avoidance behaviour leads to even greater fear and symptoms, producing more pain or fatigue [15–17].

These factors can be extended to patients with cancer-related asthenia, which is why physical activity is important to help them avoid loss-of-function and reduced physical capacity [15]. Selection of the optimal intervention environment is based on clinical complexity and the patient’s ability to self-manage their situation. Several previous studies, including a meta-analysis of 14 randomised controlled clinical trials in breast cancer survivors with an intervention supervised by phone or email [18], have shown that supervised physical exercise interventions outside the healthcare provision environment, both in the community and at home, have had good results.

However, despite the potential benefits of such interventions, there is little evidence available on the possible effects that multimodal physical exercise and functional rehabilitation programs may have on patients with cancer-related asthenia outside healthcare settings. Thus, this present clinical trial was designed to address this research gap and to create empirical evidence regarding the effect of an interdisciplinary multimodal physical exercise and functional rehabilitation program intervention applied at the time of hospital discharge in patients with cancer-related asthenia.

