### Procedures and data collection

#### Evaluations and study plan

Participants will be assessed at three points during the study: Firstly, the baseline assessment at the beginning, the second assessment after seven days, and a third final assessment, before the patients are discharged from hospital. The baseline assessment will be performed after recruitment and before randomisation and assignment of subjects to the corresponding group. This initial assessment includes the recording of the independent variables and the primary and secondary outcome variables of the study. Then, after randomisation, the corresponding intervention will begin to be applied to each group. Subsequently, the other further assessments will be carried out, one after seven days, considered as the follow-up assessment, and another at hospital discharge, considered as the final assessment. This can be seen in more detail in Table 1.

**Table 1 Tab1:** Timeline and dimensions assessed at the time points

	STUDY PERIOD							
	**Enrolment**	**Allocation**	**Post-allocation**					**Close-out**
**TIMEPOINT**	***Month 1-2***	***Month 2-3***	***M4***	***M5***	***M6***	***M7***	***M8***	***M9-M12***

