#### Interventions

Conventional standard of care will be applied in both groups, explaining to each subject participating in the study the importance of compliance and adherence to the prescribed pharmacological treatment and the established guidelines personalised to their specific health needs. In the days prior to hospital discharge, they will also receive, as a part of the intervention, a health education programme with an informative talk and written guidelines, mainly focused at reinforcing and promoting an active and healthy lifestyle.

The difference of the intervention in the experimental group will be due to the fact that we will also implement the intervention with a multimodal programme of physical exercise and functional rehabilitation lasting one month. This will consist of:

1. A prescription for multimodal physical exercise. In the Oncology Hospitalisation Unit at the CAUSA, as in other studies already initiated [19], we will carry out the following design of a multimodal physical exercise programme. A supervised and structured program will be implemented in these patients for one month. This will consist of two short 15–20-minute sessions performed daily, one in the morning and one in the afternoon. The sessions will be structured according to the recommendations of the American College of Sports Medicine (ACSM) [29, 30], with an initial warm-up (2–3 min), the main section comprising the principal physical exercises (8–12 min), and a final cool-down and relaxation phase (5 min).

Parts of a standard session: The warm-up will consist of exercises designed to promote joint mobility and muscle activation. The main section will combine aerobic and balance exercises with low-load strength exercises targeting upper and lower quadrant muscle groups. The dosage and load will always be adapted according to patient evaluations performed beforehand and will follow a progression in difficulty with the aim of achieving an intensity at 50–75 % of each patient’s maximum heart rate or a perception of moderate effort on the Borg Scale. After 15 days of the program, the second evaluation will be carried out and the program may then be modified by adapting the load. Finally, the cool down will consist of gentle muscle stretching and relaxation exercises.

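### The final assessment at discharge conflicts with a one-month programme evaluated at 15 days and 1 month, and the article does not settle whether exercise starts at randomisation or after discharge

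*Protocol article*

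**What the plan says.** **Assessment times.** Evaluations and study plan lists three assessments: a baseline, then "the second assessment after seven days, and a third final assessment, before the patients are discharged from hospital". It repeats the last of these as "another at hospital discharge, considered as the final assessment". Interventions describes two exercise sessions a day for one month and says "After 15 days of the program, the second evaluation will be carried out", at which point the load may be adapted. Work plan and visit structure also has three visits, but places the second and third at 15 days and 1 month from the first, with telephone contact at 3 and 6 months from randomisation. The section on the follow-up visits holds them at a university unit outside the ward. Both schedules point to Table 1, which is laid out in study months and does not settle timing for the individual patient.

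**Start and place of the programme.** Evaluations and study plan says "Then, after randomisation, the corresponding intervention will begin to be applied to each group". Baseline visit puts randomisation at the end of a visit made before discharge. Interventions introduces the exercise with "In the Oncology Hospitalisation Unit at the CAUSA, as in other studies already initiated [19], we will carry out the following design". The Discussion instead says "our study proposes a supervised home-based intervention adapted to the specific situation of each patient with moderate cancer-related asthenia for implementation after their discharge". The Background names the research gap as the effects that "functional rehabilitation programs may have on patients with cancer-related asthenia outside healthcare settings", and describes the trial's own intervention as a "program intervention applied at the time of hospital discharge in patients with cancer-related asthenia". The Conclusions also place the programme in follow-up after discharge.

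**The concern.** The Barthel Index is the main variable, and its last planned score should reflect the programme under test. A final assessment tied to discharge has no fixed relation to the end of a one-month programme. It comes early for everyone whose remaining stay is shorter than a month, and the amount of exercise received by then varies with length of stay. If exercise begins only after discharge, that assessment comes before any of it. The primary comparison would then reflect the inpatient training in daily activities and the assistive products, not the exercise.

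A second, lesser matter is the scope of the conclusion. The Background motivates the trial by a lack of evidence outside healthcare settings. If the month starts at randomisation of inpatients, part of the exercise is given on the ward, and the article does not say how much.

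**Working it through.** The plan gives no figure on this point to reproduce, so the check crosses the two possible starts of exercise with the two final-assessment times.

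**Inputs**
- Sessions per day: 2 (Interventions).
- Duration: one month (Interventions), assumed 30 days. Total = 2 × 30 = 60 sessions (56 for 28 days, 62 for 31 days).
- Remaining stay after randomisation, L days: not given, so assumed. Under the discharge schedule the seven-day assessment precedes the final one, so L is at least 7; the upper value used is 20. Under the 15-day and 1-month schedule no minimum is implied; 5 to 20 is used.

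**Second assessment.** At 7 days from a start at randomisation, 2 × 7 = 14 of 60 sessions are scheduled. At 15 days, 2 × 15 = 30 of 60. Each schedule has only three assessments, so day 7 and day 15 cannot both be the second.

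**Exercise scheduled by the last Barthel score**

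| Exercise starts | Final assessment | Days of 30 | Sessions of 60 |
|---|---|---|---|
| Randomisation | Discharge | L | 2L: 14 (L = 7) to 40 (L = 20) |
| After discharge | Discharge | 0 | 0 |
| After discharge | 1 month from baseline | 30 − L | 2(30 − L): 50 (L = 5) to 20 (L = 20) |
| Randomisation | 1 month from baseline | 30 | 60 |

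First row as percentages: 14/60 = 23% and 40/60 = 67%. With a month of 31 or 28 days, the 7-day figure is 14/62 = 23% or 14/56 = 25%. The row reaches 60 only when L is 30.

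Only the last row measures the completed programme whatever the length of stay.

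**Which start the text favours.** The second evaluation falls 15 days into the programme (Interventions) and also 15 days after the first visit (Work plan and visit structure). These agree only if the programme starts at about the baseline visit, that is, at randomisation. The Discussion sentence does not fit that start unless it describes only the part delivered after discharge, which it does not say.

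**The case against.** The strongest reply is that most of the text supports one coherent plan, with the seven-day and discharge schedule as the outlier. Baseline and randomisation come before discharge, the package starts in hospital, exercise continues at home, and visits follow at 15 days and 1 month at an outpatient site. The intervention that begins after randomisation includes training in daily activities and the assessment for assistive products, both given before discharge, so that sentence need not mean that exercise begins then. Naming the Oncology Hospitalisation Unit may identify the team that runs the programme and not the place of each session. These replies stand. They show that place and start can largely be reconciled.

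A reader might infer that the last Barthel score will precede all exercise. That requires joining the Discussion sentence to the discharge schedule while setting aside the statement in Interventions that the second evaluation falls 15 days into the programme. It is one possible combination, and the documents do not support presenting it as the plan. A reader might also infer that a mix of ward and home sessions biases the randomised comparison. It does not; it limits only what can be claimed about delivery outside hospital.

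The reply does not remove the schedule conflict. Even under the ward-then-home reading, a final assessment at discharge comes before the end of a one-month programme unless the patient stays a month. The telephone contacts do not help, because they belong to the other schedule. Nor is this detail left to a fuller protocol: the article states both schedules.

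**Conclusion.** The point holds as a conflict between stated schedules, with an unstated start and setting alongside it. If the discharge schedule is followed, the last Barthel score is taken before the programme is complete for any patient discharged within a month of randomisation. With a start at randomisation, that is after 14 of 60 sessions for a 7-day stay and 40 of 60 for a 20-day stay. If exercise starts only after discharge, it is after none, but this is the conditional worst case. If the month starts at randomisation and the 15-day and 1-month visits hold, the Barthel comparison covers the whole programme and only the out-of-hospital claim needs care.

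The session counts rest on a 30-day month, full delivery of two sessions a day, and assumed lengths of stay. The conflict itself rests on none of these. No effect on power or on the size of the estimate is claimed.

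**What to change.** - In Interventions, state that the month starts at randomisation, with sessions on the ward until discharge and at home afterwards.
- In Evaluations and study plan, replace the seven-day and discharge assessments with the 15-day and 1-month visits counted from the baseline visit.
- Align the Discussion sentence with that sequence.
- Record each patient's discharge date, and limit any out-of-hospital claim to what was delivered after it.

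The cost is protocol wording, one date per patient and possibly a narrower claim. A ward or home entry for each session is optional. Anchoring both programme and visits to discharge would also remove the conflict, but the time from randomisation to assessment would then depend on length of stay, which could differ between arms. A start at randomisation is therefore preferable.

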## Limitations

This study will follow all the recommendations of the CONSORT guidelines, but due to the nature of the intervention itself, the participants will not be blinded to the intervention. However, the researchers responsible for carrying out the study measurements in each evaluation and for the statistical analysis will be blinded.

### Dissemination plan

Dissemination of the study results will be carried out with the intention of ensuring maximum visibility. The results will be published in peer-reviewed open access scientific journals. There will be an initial publication of the primary results, with further publications of the secondary results planned. The results will also be presented at major national and international scientific conferences and seminars. Finally, the research team and the Oncology Hospitalisation Unit at the CAUSA will disseminate the results in social networks and other media.

### How potential changes in the study will be approached

Significant modifications to the protocol (such as change in the tools of evaluation, modifications to the selection criteria or to the interventions) will be communicated immediately to the bioethics committee.

## Conclusions

This study protocol aimed at assessing the influence of incorporating an interdisciplinary intervention, carried out by nurses, occupational therapists, physiotherapists, and specialist doctors in patients with cancer-related fatigue, with the aim of improving conventional clinical practice, and introducing a program of multimodal physical exercise and functional rehabilitation, which we consider essential in the follow-up of patients once they are discharged from hospital.

## Data Availability

Upon completion of the study, the datasets generated and/or analysed during the current study will be available to those investigators who request it through FAIRsharing of the repositories of research data at https://www.re3data.org/.

## Abbreviations

SPPB: Short Physical Performance Battery
NCCN: National Comprehensive Cancer Network
VAS: visual-analogue scale
MMSE: Mini-Mental State Examination
BI: Barthel Index
HRQoL: Health-related quality of life
TSK-F: Tampa Scale for Kinesiophobia associated with Fatigue
FACT-An: Functional Evaluation of Cancer Therapy-Anaemia
TMT: Trail-Making Test
EQ-5D: EuroQol 5-D Questionnaire
ACSM: American College of Sports Medicine
ADL: Activities of daily living
